### Randomization and blinding

2.7

The random method will use the closed envelope method for block randomization. Use the SAS software PROC PLAN procedure statement for random grouping. The subjects will be numbered 1 to 64 according to the order in which the patients were enrolled, and random numbers and assignments corresponding to the order of inclusion were obtained. The groups will be sealed in opaque envelopes, and the order of inclusion will be affixed to the surface of the envelopes. Randomization envelopes and distributions are performed by individuals who are not involved in treatment and evaluation.

### Statistical analysis

2.8

According to the m-ITT principle, all randomized cases will be included. And there is at least one treatment and one post-baseline data. The missing data are not filled, and the actual observation values are used for statistical analysis. The measurement data are described by mean, standard deviation, median, and quartile. If the data meets the normal distribution, it is compared with the baseline value at the time of enrollment, and a paired *t* test is used. Differences in efficacy between the two groups will be compared using independent sample *t* tests. If the normal distribution is not satisfied, a non-parametric test is used. The count data is described using a composition ratio. If the normal distribution is satisfied, the changes before and after treatment in the two groups are tested by *X*^2^. If the normal distribution is not satisfied, a non-parametric test is used. The statistical software is SPSS 24.0, when *P* < .05, it showed that the difference is statistically significant.

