#### Criteria for termination of trials

2.3.4

If the following happens, we will terminate the test: severe acute disease response, severe allergic reactions, and other adverse reactions; those who withdraw due to worsening or ineffective eye disease during treatment.

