#### Primary outcome measures

2.5.1

*Fundus fluorescein angiography*. Inspection method: Tobiconamide eye drops in the conjunctival sac are fully dilated. Perform allergy tests on patients according to reagent requirements. If you are not allergic, push the sodium fluorescein stock solution into the vein and observe the patient's retinal vein filling with the fundus camera. Check before and after treatment.

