#### Secondary outcome measures

2.5.2

Observe the best corrected vision before and after treatment. Check with international standard eye chart. The visual acuity chart is 5 m away from the subject. During the inspection, the two eyes are performed separately. One eye is covered. Observe the changes of the fundus before and after treatment. Tobicalamide eye drops in the conjunctival sac were fully dilated, and the fundus camera was used to photograph the patient's fundus.

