#### Efficacy evaluation

2.5.3

Refer to “Guidelines for Clinical Research of New Chinese Medicine”. Efficacy was evaluated by the ratio of the difference between the points before and after treatment compared to the points before treatment. Syndrome treatment efficiency (%) = (total points before treatment total points after treatment)/total points before treatment × 100.

(1)Clinical control: clinical symptoms and signs disappeared or basically disappeared, and syndrome scores were reduced by ≥95%;(2)Significant effect: clinical symptoms and signs were significantly improved, and syndrome scores were reduced by 70%;(3)The signs and symptoms have improved, and the syndrome scores have decreased by ≥30%;(4)Ineffective: the clinical symptoms and signs have not improved significantly, and the syndrome scores have decreased by <30%.

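### Under section 2.8, patients who withdraw for worsening or lack of effect without a later examination leave the efficacy comparison and are not counted as 'Ineffective'

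*Protocol article*

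**What the plan says.** Section 2.8 (Statistical analysis) opens with "According to the m-ITT principle, all randomized cases will be included". The next sentence restricts the set: "And there is at least one treatment and one post-baseline data". It then fixes the missing-data rule: "The missing data are not filled, and the actual observation values are used for statistical analysis".

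Section 2.3.4 lists, among the grounds for ending the trial for a patient, "those who withdraw due to worsening or ineffective eye disease during treatment".

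The efficacy measures are timed as follows:

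- Fluorescein angiography (FFA), the primary outcome, section 2.5.1: "Check before and after treatment".
- Corrected vision, section 2.5.2: "Observe the best corrected vision before and after treatment".
- Fundus photography, section 2.5.2: "Observe the changes of the fundus before and after treatment".
- Syndrome score, section 2.5.3: "Efficacy was evaluated by the ratio of the difference between the points before and after treatment compared to the points before treatment". Category 4, 'Ineffective', is a fall in score below 30%.

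Treatment lasts three back-to-back 4-week courses (section 2.4). That section also asks for the patient's condition to be watched closely, but names no interim efficacy measurement. Section 2.6 allows for drop-out of up to 20%.

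**The concern.** Each rule is unremarkable alone. Together they tie missing data to the outcome. The patients whom section 2.3.4 expects to leave are those doing badly, and the text gives them no examination on leaving. Without one they have no post-baseline value, so they fail the condition for the m-ITT set, and nothing is imputed for them. The 'Ineffective' category cannot hold them either, because it is computed from a score after treatment.

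What is at stake is the main efficacy comparison. Removing failures makes each arm look better than it was. If one arm loses more failures than the other, that arm gains more from the rule, and a difference can appear, shrink or change sign for reasons unrelated to efficacy. With 32 patients per arm, a few withdrawals are enough to matter.

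**Working it through.** The plan gives no figure for failure withdrawals, so there is none to reproduce. The check first follows a patient through the rules and then illustrates the size.

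**Path of a patient who withdraws for failure**

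1. The patient is randomised, treated, and withdraws during the 12 weeks (section 2.3.4).
2. If not examined again, the patient has baseline values only (sections 2.5.1 to 2.5.3).
3. The condition of a post-baseline value is not met, so the patient is outside the m-ITT set (section 2.8).
4. Nothing is imputed, and no rule assigns the patient to category 4 of section 2.5.3.

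If the patient is examined on leaving, step 2 fails and the patient stays in the set.

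**Inputs from the documents.** 32 patients per arm (sections 2.4 and 2.6). Drop-out of up to 20%: 0.20 × 64 = 12.8, so at most 12 whole patients. This ceiling covers all causes.

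**Inputs assumed.** The true response rate and the number of failure withdrawals in each arm.

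**Formula.** With r true responders among n randomised and w failures withdrawn unexamined, the observed-case rate is r/(n − w). The rate with those withdrawals counted as failures is r/n.

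**Illustration 1: true response 60% in both arms, 8 failure withdrawals in total** (8/64 = 12.5%). r = 32 × 0.60 = 19.2 per arm.

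| Withdrawn failures | Observed-case rates | Apparent difference |
|---|---|---|
| 6 and 2 | 19.2/26 = 73.8%; 19.2/30 = 64.0% | 9.8 points |
| 4 and 4 | 19.2/28 = 68.6% in both | 0 |

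Counting withdrawals as failures gives 60% in both arms in either row. The false gap favours the arm that lost more failures.

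**Illustration 2: 16 of 32 respond in both arms, 12 failure withdrawals in total** (12/64 = 18.75%).

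| Withdrawn failures | Observed-case rates | Apparent difference |
|---|---|---|
| 6 and 6 | 16/26 = 61.5% in both | 0 |
| 9 and 3 | 16/23 = 69.6%; 16/29 = 55.2% | 14.4 points |

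**Illustration 3: a real difference.** Let 19 of 32 respond in arm A and 16 of 32 in arm B: 59.4% − 50.0% = 9.4 points.

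- If A loses 3 failures and B loses 9, observed cases give 19/29 = 65.5% against 16/23 = 69.6%, so the sign reverses (−4.0 points).
- If each loses 6, they give 19/26 = 73.1% against 16/26 = 61.5%, or 11.5 points. Equal losses leave the direction alone but stretch a real difference slightly.

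**Type I error.** This was simulated with 400,000 trials, 32 per arm, 50% true response in both arms, 20% overall drop-out made up entirely of failures, and a pooled two-proportion z test at a nominal two-sided 5%.

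| Probability that a failure withdraws, by arm | Observed cases | Withdrawals counted as failures |
|---|---|---|
| 40% and 40% | about 5% | about 6% |
| 50% and 30% | about 9% | about 6% |
| 60% and 20% | about 22% | about 6% |

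All these figures concern a binary response, as the categories of section 2.5.3 would supply. They do not carry over directly to FFA, for which the text gives no scale or responder definition.

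**The case against.** The strongest objection is that the text does not say the outcomes are measured *only* before and after treatment. The visit schedule is in Figure 1, which could not be seen here and may hold interim or exit visits. Section 2.8 speaks of at least one post-baseline value, which leaves room for more than one. The after-treatment examination is not tied to week 12, so for a patient who stops early it could be done on stopping. This stands as a limit. The point applies to patients who leave without a later examination, and an exit visit in Figure 1 would shrink their number.

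A reader might infer that section 2.3.4 removes every non-responder and that the analysis is therefore a completers' analysis. The text does not support that. It describes patients who withdraw. A non-responder who stays is measured and falls in category 4.

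A reader might also infer that the comparison is certainly biased, or biased towards the intervention. That is not supported either. The response rates and splits above are assumed, the 20% in section 2.6 is drop-out from any cause, and nothing in the document says which arm would lose more failures. Equal withdrawal cannot be taken for granted, though: the trial is only single-blind (section 2.1), and one arm takes capsules and the other an oral solution (section 2.4).

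The opening two sentences of section 2.8 can be read as one awkwardly worded definition of m-ITT. That is fair, so the conflict between them is a matter of wording.

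Finally, the analysis plan might settle the matter. It could add detail, but section 2.8 already fixes both the analysis set and the no-imputation rule, and the objection is to those stated choices.

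**Conclusion.** The concern holds in a conditional form. As written, section 2.8 excludes patients who withdraw for worsening or lack of effect and are not examined afterwards, and no rule counts them as 'Ineffective'. Response rates in each arm are then too high. With no true difference between arms, a false one arises only if these withdrawals are unequal: about 10 points for 6 against 2 at an assumed 60% response, and zero for 4 against 4. The direction cannot be predicted from the document. How often this would happen depends on whether Figure 1 contains interim or exit examinations; the text states none. Because the remedy is cheap and the rule concerns the main comparison, it is worth changing before any outcome data are seen.

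**What to change.** In section 2.8:

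1. Analyse the response outcome in all randomised patients by assigned arm, and reword the opening sentences so that the description and the set agree.
2. Count withdrawal for worsening or lack of effect as 'Ineffective' (category 4 of section 2.5.3).
3. State that the end-of-treatment assessments already planned are done at withdrawal where the patient is available.
4. Keep the observed-case analysis as a sensitivity analysis.
5. Add a sensitivity analysis for patients missing for other reasons, such as adverse reactions or loss to follow-up, since step 2 does not cover them.

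For FFA, withdrawals for failure could be given the worst rank, but only if an FFA scale is first defined.

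The cost is a few sentences, slightly less favourable response rates and a little more analysis. The exit examinations are moved forward rather than added. For a patient who would otherwise have left unexamined, however, FFA still means an allergy test and an intravenous injection, so it depends on the patient's agreement.

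### The between-arm t test leaves out the baseline values already collected; for numerical outcomes, a baseline-adjusted analysis would usually be more precise at small cost

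*Protocol article*

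**What the plan says.** Section 2.8 (Statistical analysis) fixes the between-arm method for measurement data: "Differences in efficacy between the two groups will be compared using independent sample" t tests, with a non-parametric test if normality fails. No covariate is named. Baseline appears only in a separate comparison of post-treatment data with enrolment: "it is compared with the baseline value at the time of enrollment, and a paired" t test is used. For count data, "the changes before and after treatment in the two groups are tested by" a chi-square test, again with no adjustment.

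The outcome sections show that a baseline is always taken:

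- Section 2.5.1, fluorescein angiography (FFA, the primary outcome): "Check before and after treatment". No numerical measure is named.
- Section 2.5.2, acuity: "Observe the best corrected vision before and after treatment. Check with international standard eye chart". No analysis scale is named.
- Section 2.5.2, fundus photography: "Observe the changes of the fundus before and after treatment". No scale is named.
- Section 2.5.3, syndrome score: "Efficacy was evaluated by the ratio of the difference between the points before and after treatment compared to the points before treatment". The result is then graded in four categories.

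Sections 2.6 and 2.7 give 32 patients per arm, dropout of up to 20%, and block randomisation with no stratification factor stated.

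**The concern.** A paired test within each arm describes change over time but does not compare treatments. The treatment comparison rests on the independent-sample test, which uses baseline at most indirectly, through a change or a percentage.

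Blocking balances the number of patients per arm, not their severity at entry. In a trial this small the arms can differ noticeably at baseline by chance, and an unadjusted estimate carries part of that difference into the result. It also leaves in the error term whatever follow-up variation the baseline could explain. What is at stake is the width of the confidence interval and the chance of detecting a real difference. The data needed to improve both are already being collected.

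**Working it through.** **Inputs from the protocol article.** 32 per arm, 64 in total, dropout up to 20% (section 2.6); block randomisation, no stratification stated (section 2.7); significance at 0.05 (section 2.8), taken here as two-sided.

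**Inputs assumed.** The protocol gives no SD, effect size, power or baseline-to-follow-up correlation rho. I take rho from 0 to 0.7, SD = 1 at both times, and a linear baseline-outcome relation.

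**The plan's own figure.** No precision or power is stated, so there is none to reproduce. The total of 64 rests on a minimum of 30 per arm. It does not follow from that minimum and 20% dropout (30/0.80 = 37.5, so 38 per arm or 76 in total), but nothing below depends on this. With 20% loss, 32 × 0.80 = 25.6, or about 26 per arm.

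**Step 1: chance imbalance.** The SD of the between-arm baseline difference is √(2/n). At n = 32 this is √(2/32) = 0.25 SD units; at n = 26 it is √(2/26) = 0.28. An imbalance beyond 0.25 SD in either direction therefore occurs in about 32% of trials of 32 per arm.

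**Step 2: what an imbalance does.** An imbalance of b shifts a final-value comparison by rho × b and a change comparison by (rho − 1) × b. With b = 0.25:

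| rho | Shift, final values | Shift, change |
|---|---|---|
| 0.3 | +0.075 | −0.175 |
| 0.5 | +0.125 | −0.125 |
| 0.7 | +0.175 | −0.075 |

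ANCOVA removes these shifts if the relation is linear.

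**Step 3: relative variance.** Final values: 1. Change: 2(1 − rho). ANCOVA with one random baseline covariate: (1 − rho²) × (1 + 1/(N − 4)). At N = 64 the small-sample factor is 1 + 1/60 = 1.017.

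Example at rho = 0.5: 0.75 × 1.017 = 0.76. Change has variance 2 × 0.5 = 1, so the ratio is 0.76 against either test.

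| rho | ANCOVA / final values | ANCOVA / change |
|---|---|---|
| 0 | 1.02 | 0.51 |
| 0.3 | 0.93 | 0.66 |
| 0.5 | 0.76 | 0.76 |
| 0.7 | 0.52 | 0.86 |

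At 26 per arm the ratios differ by no more than about 0.01.

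**Step 4: break-even.** ANCOVA beats final values when (1 − rho²) × 61/60 < 1, that is rho² > 1/61, or |rho| above about 0.13 (about 0.14 at N = 52). It beats change at every rho tried.

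**Step 5: power, for scale.** Take an assumed standardised difference of 0.70, which gives 80% power at 32 per arm by the normal approximation: (1.96 + 0.84) × 0.25 = 0.70. Power from the noncentral t is:

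| rho | Final values | Change | ANCOVA |
|---|---|---|---|
| 0 | 78.8% | 49.6% | 78.1% |
| 0.3 | 78.8% | 64.5% | 81.8% |
| 0.5 | 78.8% | 78.8% | 88.4% |
| 0.7 | 78.8% | 94.5% | 96.9% |

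**Not computed.** Precision relative to a t test on percent reduction depends on the distribution of baseline scores, which the protocol does not give.

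**The case against.** The strongest reply is that nothing here is wrong. An independent-sample t test is valid in a 1:1 randomised trial, and its type I error already allows for chance imbalance. That stands. A reader might infer a biased test or an inflated false-positive rate, and the protocol does not support that inference. Covariate adjustment might also be left to a fuller plan, but section 2.8 does state a method, and it is the stated method that can be improved.

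A reader might also infer that baseline is ignored altogether. The text does not establish this. Section 2.5.3 defines efficacy as a reduction relative to baseline, so a test of change or percent reduction is at least as natural a reading as a test of final values. On the change reading the gain is smaller at high rho: about 14% lower variance at 0.7, against 48% relative to final values.

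Nor does the remedy reach every outcome. FFA, the primary outcome, and fundus appearance have no numerical scale as written, and the four-grade result is a category. ANCOVA cannot be fitted to these.

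The adjustment is not quite free, and its benefit depends on an unstated rho. At rho 0.3 the variance reduction against final values is only about 7%, and at rho 0 there is a small loss.

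Two further inferences are tempting. One is that acuity will be analysed as decimals, so that equal steps are unequal on a log scale; the protocol names a chart but no recording scale. The other is that the percent reduction will meet a zero baseline score; the scoring items are not shown, and patients must meet the diagnostic criteria to enter. Neither is needed for the point.

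**Conclusion.** The point holds as a matter of efficiency for numerical outcomes. The planned between-arm test is valid but unadjusted, and it leaves unused, or uses less efficiently, a baseline that is already measured for acuity and the syndrome score. At an assumed rho of 0.5, ANCOVA has about 24% lower variance than a t test on either final values or change. Over rho from 0 to 0.7, the result against final values runs from about 2% worse to 48% better, and against change from 49% to 14% better.

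These sizes assume equal SD before and after treatment, a roughly linear relation and the rho values shown, none of which the protocol supplies. The direction is more secure than the size: ANCOVA was better than change at every rho tried, and it is better than final values once |rho| exceeds about 0.13. For FFA and fundus appearance the point applies only once a numerical measure is defined.

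**What to change.** Amend section 2.8 so that, for each numerical outcome, the between-arm analysis is an ANCOVA of the end-of-treatment value with arm and baseline value as terms, reported as the adjusted difference with its 95% CI. Apply it to:

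- best corrected vision, on a logMAR scale stated in section 2.5.2;
- the absolute syndrome score, keeping the percent-reduction grades of section 2.5.3 as supporting description;
- any numerical FFA or fundus measure, once one has been defined in sections 2.5.1 and 2.5.2.

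Base treatment conclusions on this contrast and keep the within-arm paired tests as description. Make the change before any unblinded data are seen.

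The cost is a change of wording with no new data, one degree of freedom, about 2% more variance if rho is near 0 (power 78.1% against 78.8% in the example), and reliance on a roughly linear baseline-outcome relation.

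### The count-data rule makes chi-square depend on normality, which cannot select a test, and names no test that uses the order of the four efficacy grades

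*Protocol article*

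**What the plan says.** All statements are in the protocol article.

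- **Section 2.8, Statistical analysis, count data.** "The count data is described using a composition ratio". The test follows: "If the normal distribution is satisfied, the changes before and after treatment in the two groups are tested by" chi-square. The other branch reads "If the normal distribution is not satisfied, a non-parametric test is used", the same sentence that closes the rule for measurement data. No test is named in it.
- **Section 2.8, measurement data.** Here pairing is recognised: under normality "it is compared with the baseline value at the time of enrollment, and a paired" t test is used. Between-group differences in efficacy go to an independent-sample t test. No paired counterpart is given for counts.
- **Section 2.5.3, Efficacy evaluation.** "Efficacy was evaluated by the ratio of the difference between the points before and after treatment compared to the points before treatment". That percentage is then cut into four ordered grades. The top one is "Clinical control: clinical symptoms and signs disappeared or basically disappeared, and syndrome scores were reduced by ≥95" per cent and the bottom one is "Ineffective: the clinical symptoms and signs have not improved significantly, and the syndrome scores have decreased by <30" per cent, with two grades between.
- **Section 2.5.1.** The primary outcome is fundus fluorescein angiography. The four grades are listed neither there nor among the secondary outcomes in section 2.5.2.

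**The concern.** The normality switch written for measurement data has been carried over to count data, where it has no meaning. A category membership has no normal distribution to satisfy, and Pearson chi-square does not require one. A trial statistician therefore cannot apply the rule as written. Either every count outcome falls to an unnamed test, or the condition is ignored and chi-square is used.

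In the second case the test does not suit the one categorical outcome that is defined, because a 4×2 chi-square treats ordered grades as unordered labels. The phrase about changes before and after treatment also leaves open whether the comparison is between arms (independent patients) or within an arm (the same patients twice). At stake are power on the efficacy grade in a trial of 64 patients, and a choice of test left open until the data have been seen.

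**Working it through.** The plan states no figure for this point, so there is none to reproduce. The check has a logical part and an illustrative part.

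**1. Logic of the rule.** Section 2.8 gives two branches: normal, then chi-square; not normal, then an unnamed test. Counts in categories are never normal, so the first branch is empty when read literally.

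**2. Inputs for the illustration.** From the documents: 32 per arm (section 2.6) and a significance threshold of .05, at which "it showed that the difference is statistically significant" (section 2.8). Two-sided testing is assumed, because sidedness is not stated. Grade rates, odds ratios and within-patient correlations are assumptions, because the article gives none.

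**3. Four grades between arms.** The treated arm follows a common odds ratio (OR): each cumulative odds, counted from the worst grade, is the control odds divided by OR. Example for set A, with control grades 30/35/25/10% from worst to best:

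- Cumulative control rates are 0.30, 0.65 and 0.90, so the odds are 0.429, 1.857 and 9.
- At OR 3 these become 0.143, 0.619 and 3, so the cumulative rates are 0.125, 0.382 and 0.750.
- The treated grades are therefore 12.5/25.7/36.8/25.0%.

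Set B has control grades 30/40/25/5% from worst to best. Simulated power at 32 per arm:

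| Set | OR | Chi-square (3 df) | Wilcoxon rank-sum | Loss |
|---|---|---|---|---|
| A | 2 | 0.22 | 0.33 | 0.11 |
| A | 3 | 0.50 | 0.67 | 0.17 |
| A | 4 | 0.68 | 0.85 | 0.17 |
| B | 2 | 0.20 | 0.31 | 0.11 |
| B | 3 | 0.47 | 0.65 | 0.18 |
| B | 4 | 0.68 | 0.84 | 0.16 |

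Set A used 3,000 replicates per scenario. A separate run of set B with 6,000 replicates gave 0.46 against 0.64 at OR 3 and 0.69 against 0.85 at OR 4.

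With no effect, rejection rates were 0.053 (chi-square) and 0.056 (Wilcoxon) in set A, and 0.047 and 0.051 in set B. Chi-square therefore roughly keeps its level.

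If 20% drop out, 32 × 0.8 = 25.6, or about 26 per arm. Set B at OR 3 then gives 0.39 against 0.58.

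**4. Sparse cells.** With equal arms, the expected count in a cell is half its column total. In the top grade with no effect this is 32 × 0.10 = 3.2 in set A and 32 × 0.05 = 1.6 in set B. At OR 3 in set A it is 32 × (0.10 + 0.25)/2 = 5.6. The share of simulated trials with at least one expected count below 5 ran from 26% to 98%, depending on the rates.

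**5. If before/after counts within an arm are meant.** For a binary finding with rate p at both times and correlation ρ, the variance of the difference in proportions is 2p(1−p)(1−ρ)/n. Unpaired chi-square uses 2p(1−p)/n, which is too large when ρ > 0. At ρ = 0.5 the effective critical value is 1.96/√0.5 = 2.77, a two-sided level of about 0.006. Simulation with n = 32 and 5,000 replicates:

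| ρ | Level at p = 0.5: chi-square | Level: McNemar | Power for 60% to 40%: chi-square | Power: McNemar |
|---|---|---|---|---|
| 0.3 | 0.024 | 0.046 | 0.36 | 0.44 |
| 0.5 | 0.010 | 0.045 | 0.34 | 0.60 |
| 0.6 | 0.004 | 0.046 | 0.32 | 0.74 |

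The McNemar columns use the asymptotic version. The exact version is itself conservative, with a level of 0.0165 at n = 32 and ρ = 0.5 in a separate run.

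**The case against.** The strongest defence is that the literal rule does no harm. If counts are never normal, the fallback applies, and for ordered grades the unnamed non-parametric test could be the rank-sum test recommended here. Naming that test is a detail that an article may leave to the analysis plan. This stands in part: it is wrong to say that the rule, followed literally, produces chi-square p-values. It does not save the condition, which is stated, is meaningless for counts, and would be inherited by any analysis plan that follows it.

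Other points on that side also stand:

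- A reader might infer that the plan applies unpaired chi-square to paired counts. The document does not establish this. The grade is one value per patient, so comparing it between arms involves independent observations, and the sentence can be read that way. No paired binary endpoint is defined, so the paired results above are conditional on a reading that may not be the intended one.
- A reader might infer a risk of false positives. None is shown: between arms the level is about right, and in the paired case the error is conservative.
- A reader might infer that expected counts below 5 are nearly certain. They range from occasional to almost universal with the assumed rates.
- Section 2.8 sends differences in efficacy to a t test with a non-parametric fallback. If the percentage change itself is analysed that way, the ordering is already used. The article does not say that count data means the four grades. They are, however, the only categorical outcome it defines.

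**Conclusion.** The concern holds as a fault in a stated rule. Normality cannot decide between tests for categorical counts. The rule therefore either never reaches chi-square or, where chi-square is used, discards the order of the four-grade response.

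For the between-arm comparison the cost is power, not validity: about 11 to 18 percentage points against the Wilcoxon rank-sum test for odds ratios 2 to 4 at 32 per arm, with the type I error at roughly 0.04 to 0.06. These figures rest on assumed grade rates and a proportional-odds effect. For a before/after comparison within an arm, unpaired chi-square would be unsuitable and conservative, but the wording leaves open whether that comparison is planned.

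This is a should-fix. Rating it as essential would treat the grade as the main result, and section 2.5.1 names angiography as the primary outcome.

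**What to change.** In section 2.8, delete the normality condition for count data and name the tests by type of data:

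- **Four-grade response between arms:** Wilcoxon rank-sum test, or a proportional-odds model with the odds ratio and 95% confidence interval.
- **Any binary outcome between arms:** Fisher's exact test, with a risk difference and 95% confidence interval.
- **Any within-patient binary change:** McNemar's test, stating whether the exact or asymptotic version is used.

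State also whether count data means the four grades, and whether the comparison is between arms or within an arm. The cost is a rewrite of the count-data sentences. The tests are standard, and no additional data or patients are needed. The change should be made before unblinding.
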